### 2.10. Demographic and Clinical Information

Basic demographic information (age, sex) will be collected from peer workers.

The following information will be collected from farming community participants:-Demographic—age, sex, postcode, residential status, employment status, indigenous status, culturally and linguistically diverse status, occupation in the farming community.-Clinical—self-reported long-term health conditions, previous depression treatments.

### 2.11. Sample Size

The intended sample size is 40 participants (approximately 20 in the intervention supported by 10 peer workers and 20 in the control groups). Sample size calculations are not appropriate for feasibility trials, and a sample of 40 is generally considered adequate to establish that a definitive trial is feasible [29].

### 2.12. Recruitment

#### 2.12.1. Procedures for Recruiting People with Depression

Based on figures provided by Agriculture Victoria, we estimate that 69,000 people are employed in agricultural production in Victoria. Trials of Behavioural Activation are typically able to recruit around one in three people that are asked to participate [30]. We anticipate that around a third of people (approximately 23,000) in the farming community will meet our inclusion criteria and predict that around 200 potential participants will express an interest in participating in the trial. Recruitment will be monitored at our weekly trial management groups and, if fewer people than expected indicate interest, we will revise our recruitment strategy in consultation with our Community Reference Group.

#### 2.12.2. Recruitment Procedures

Advertising and promotion of the trial will be through existing National Centre for Farmer Health communication networks (social media, website, and monthly e-newsletter). Government, industry, community partners, and rural media contacts will be requested to promote the trial through their communications networks using recruitment material informed by a community consultation process. This approach should enable us to reach most members of the farming community. The number of contacts we obtain from this approach will inform the design of a definitive trial.

We will monitor recruitment rates at our weekly trial management team meetings. If we are not likely to recruit to time and target, we consider early revisions to our recruitment strategy through discussions with investigators and consultation with our community advisory group.

#### 2.12.3. Pre-Screening and Consent Procedures

Members of the farming community interested in participating in the trial will be asked to submit an expression of interest by telephone, email, or online. The researcher will contact potential participants by phone to discuss the trial in detail and to obtain verbal consent to complete screening. At the start of the screening interview, participants will be asked to complete the PHQ-9. Researchers will total the score and feedback to participants.

PHQ-9 cut-off scores from Kroenke et al. [24] will be used. Potential participants scoring below five or over 19 on the PHQ-9 will be notified that they do not meet trial inclusion criteria and are not eligible to take part in the trial. Ineligible participants will be sent a copy of the Managing Stress on the Farm self-help workbook. Ineligible participants scoring over 19 (indicative of severe depression) will be informed by the researcher that their score suggests that they may be experiencing severe depression and will be asked if they are currently receiving any psychological or pharmacological treatment for their mental ill-health. If they are, the researcher will advise the individual to contact their mental health clinician as soon as possible. In instances where the individual does not have a mental health clinician, they will be advised to contact a health professional. The researcher will explain that, due to the severity of their psychological symptoms, they do not meet trial inclusion criteria.

Potential participants that meet trial inclusion criteria will be given a detailed verbal explanation of the trial procedures and informed that they will receive an email containing a written Participant Information and Consent Form (PICF) to review and sign. If they are unable to receive the PICF via email, a paper copy will be mailed to them. If no signed PICF (electronic or paper copy) is received after 7 days, the potential participant will be followed up by phone, asking if they still wish to take part in the research.

During the consent process, participants will be informed that the information they provide will be kept strictly confidential except in circumstances where they indicate that they may harm themselves or other people. The risk of harm to self will be determined from discussion with participants.

Participants will be informed that, if they feel that they are at imminent risk of harm to self or others, they must tell the researcher, who will then advise them to contact their GP, the Emergency Department, or emergency services as appropriate.

#### 2.12.4. Inclusion of Young People Aged 15–17 Years

The prevalence of depression in young people aged 15–17 year and their early involvement in farming communities justifies their inclusion in this trial. Written consent will be sought from both young people and their parent or guardian. Including young people in the trial is informed by evidence that around a quarter of the agricultural workforce in 2021 were aged 15 to 35 years [31].

We acknowledge that depression in young people can present somewhat differently to adults [32]. For example, they may express more anger, irritability, oversensitivity to criticism or rejection, selective withdrawal, and unexplained aches and pains. However, the PHQ-9 is still considered an appropriate screening tool for adolescents [33]. For example, in a validation study involving 2235 students aged 12–18, years of age, Fonseca-Pedro [33] showed the PHQ-9 was a brief, easy, and valid screening measure in adolescents.

#### 2.12.5. Recruitment and Informed Consent Process (Peer Workers)

Peer worker positions will be advertised publicly through established National Centre for Farmer Health networks including social media and e-newsletters. Potential peer workers may also be identified through expressions of interest or via the community consultation process. Potential peer workers will apply for casual positions and will be employed by the Western District Health Service. Information about the position will include details of the research and the requirement for peer workers to participate. Applicants that meet the essential selection criteria will be invited for interview. The panel will be chaired by the chief investigator and will include two other members of the research team, including at least one lived experience researcher (with experience of living and working in a farming community). During the interview, the chair will provide a verbal description of the trial and indicate that consenting to participate in the research is a requirement of the role. Successful candidates will be offered a casual contract of employment and required to provide written informed consent to participate in the trial.

#### 2.12.6. Baseline Measures

Following consent, participants will complete week 0 (baseline) measures entered and stored on a secure password protected platform, REDCap (Research Electronic Data Capture)—a secure, web-based software platform designed to support data capture for research studies [34]. The platform is approved for use in clinical trials by both Deakin and La Trobe Universities. Participants unable to complete measures independently online will be supported by a researcher who will ask participants questions verbatim and enter responses into REDCap on their behalf. On completion of baseline measures, eligibility checklists will be finalised, and the participant will be randomised in REDCap.

Automated reminders (email and text message) will be sent 48 h and 5 days post-submission-of-consent if baseline measures are not completed. A phone call and a final reminder will be actioned on day 7. If participants fail to complete trial measures by the end of day 7, they will be informed that they have been withdrawn from the trial.

### 2.13. Allocation

Randomisation will be undertaken using an online randomisation service—Sealed Envelope Ltd London, UK [34]—and managed by the La Trobe University Clinical Trials Platform to ensure the research team remain blinded to group allocation. Randomisation will be by random permuted blocks with a 1:1 ratio.

The Clinical Trials Platform will contact the peer worker by phone and inform them of the allocation of a new trial participant and ask if there is any known conflict of interest with the allocated participant. If there is no conflict of interest, the peer worker will be provided with allocated participant details (name, telephone number, and email address) and will call the participant to introduce themselves and arrange the first session.

If there is a conflict of interest identified (either by the peer worker or participant), the participant will be reallocated to a different peer worker. Participants allocated to the control group will be contacted by phone by the Clinical Trials Platform to inform them of the allocation, emailed an electronic copy, and sent a hard copy of the Managing Stress on the Farm workbook in the post.

### 2.14. Blinding (Masking)

This is a single-blind trial. All research team members will be masked to group allocation with the exception of the Clinical Trials Platform team, who will need visibility of allocation to provide contact details to peer workers and mail resources to participants in the control group. Peer workers will be delivering the intervention and as such will not be masked.

As part of the consent process, a full explanation of the trial design will be given to participants including a description of the Back-on-Track (experimental) and Managing Stress on the Farm self-help workbook (control) interventions. Consequently, participants will not be blind to group allocation (an open-label trial). Awareness of group allocation can impact how participants respond to the intervention they receive. Participants who know they have been allocated to Back-on-Track may have more favourable expectations than those allocated to the Managing Stress on the Farm group, who may feel disappointed. Participants in the trial may assume that Back-on-Track will be better than Managing Stress on the Farm. Telling participants which intervention they will receive may also influence how participants complete outcome assessments. It is also possible that knowledge of treatment allocation may also impact participant compliance and dropout from the study. It will be important when interpreting the outcomes of this feasibility trial to acknowledge the context within which the research was conducted.

#### 2.14.1. Blinding Mechanism

Assessments will be completed online by participants or via videoconference with the assistance of a researcher who will be masked to the treatment allocation. Researcher training will include the importance of adherence to the trial protocol and maintaining blinding. For example, emphasising the importance of not asking trial participants if they received the Back-on-Track or Managing Stress on the Farm intervention (at follow-up assessments).

To test the effectiveness of allocation concealment procedures trial, researchers will be asked at the end of the trial which group they thought participants were allocated to. We will then test if the prediction was greater than chance.

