## 1. Background and Rationale

Suicide risk in farming populations is up to twice that of the general Australian population [1,2,3]. Although higher rates of diagnosed mental illness have not been clearly identified in this population [4], the association between mood and suicidal thinking seems to differ between members of the farming community and the general population. There is strong evidence for a range of situational factors (influenced by the farming context) that negatively influence farmer mental health and suicide risk [5,6,7,8,9,10].

There is some evidence that farmers are generous at providing help to others but are reluctant to ask for help themselves [11]. Most farmers live in communities in which accessing specialist mental health services is challenging [12]. Where support is available, health services and health care workers may not understand the realities of life and work in the farming environment [13]. The unique barriers to support seeking identified in farming communities may deter people from seeking help for mood problems, particularly when they have had previous negative experiences [14]. However, finding health care professionals with an understanding of farming practices and community values has been identified as an important facilitator to help seeking by Hull et al. [15].

There is sound evidence from systematic reviews of randomised controlled trials that Behavioural Activation is a safe and effective treatment for depression—a predictor of suicide [16,17]. A Cochrane review included 53 studies involving 5495 participants and concluded that there was evidence of moderate certainty that Behavioural Activation was more effective than treatment as usual [17].

Behavioural Activation is a brief psychological treatment focused on increasing behaviours that enhance mood and reducing avoidance behaviours (e.g., sitting alone and ruminating) that negatively impact mood. Unlike Cognitive Behavioural Therapy (CBT), workers without specialist mental health training can learn to deliver Behavioural Activation with minimal (typically described as around 5 days) training and ongoing supervision and support [16]. Consequently, Behavioural Activation could be delivered at-scale to people experiencing depression or low mood in communities where access to specialist mental health services is limited, such as farming communities in rural Australia.

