### 2.7. Outcomes

Outcome measures will be administered at baseline (week 0) and at weeks 10 and 26 follow-up. The primary outcome (to be used in a definitive trial) is depressive symptoms determined by change in PHQ-9 scores [24]. The PHQ-9 is a self-administered measure of depression symptoms that has been extensively used in clinical trials of psychological treatment.

Secondary outcomes (proposed) are as follows:Enhanced work performance—determined using the Work Productivity and Activity Impairment questionnaire [25], a six-item validated instrument to measure impairments in both paid work and unpaid work.Reduced loneliness—determined using the University of California, Los Angeles (UCLA) loneliness scale [26], a 20-item validated scale designed to measure the participant’s subjective feelings of loneliness as well as feelings of social isolation.Enhanced overall wellbeing—determined using the WHO-5 Wellbeing index [27], a short self-reported measure of current mental wellbeing.Improved overall quality of life—determined using the AQoL-4D [28], a validated, health-related multi-attribute utility instrument.

Outcome measures are estimated to take a total of 20 min to complete. For noting, we will not conduct or report any form of statistical analysis to determine the efficacy of the Back-on-Track intervention.

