## 3. Data Collection

### 3.1. Trial Procedures and Evaluations

Participants will be asked to complete the electronic Case Record Form (eCRF) at baseline (week 0), end of treatment (week 10), and week 26 via REDCap or with the help of a trial researcher, who will enter the information into REDCap on the participants’ behalf. Table 1 shows the notification schedule for the electronic case record form process. The participants will be considered to have withdrawn from the trial if they fail to complete outcome measures within the required time frame of 14 days or do not respond to two sequential messages from their peer worker (phone or text).

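### The end-of-trial guess test cannot tell lost masking from a working intervention, because researchers who assist follow-up assessments have already seen the answers

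*Protocol article*

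**What the plan says.** Section 2.14.1 of the Protocol article fixes three things about the check.

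- Purpose: "To test the effectiveness of allocation concealment procedures trial". The wording refers to allocation concealment, but guesses made after assignment bear on the masking of researchers.
- Timing: "researchers will be asked at the end of the trial which group they thought participants were allocated to".
- Rule: "We will then test if the prediction was greater than chance".

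On what researchers see, the same section says assessments are completed online by the participant or "via videoconference with the assistance of a researcher who will be masked to the treatment allocation". Section 3.1 says the record form may be completed "with the help of a trial researcher, who will enter the information into REDCap on the participants’ behalf". Section 2.7 says "Outcome measures will be administered at baseline (week 0) and at weeks 10 and 26 follow-up"; the measures are the PHQ-9 and four secondary scales.

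The article does not state what share of assessments will be assisted. It gives no significance level, sidedness or threshold for the test.

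**The concern.** The question of interest is whether allocation information reached the researchers. The null hypothesis tested is that guesses are unrelated to allocation. The two coincide only if the guesser has no other source of information that is correlated with allocation. A researcher who has taken a participant's week 10 and week 26 answers has such a source. Guessing Back-on-Track for those who improved beats chance whenever the intervention works, even if nothing has leaked. The article's rationale points that way: it cites a review that found "there was evidence of moderate certainty that Behavioural Activation was more effective than treatment as usual".

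Real disclosure is also possible. Participants know their arm (section 2.14), and research team members interview five participants from each group around the end of treatment (section 4.1.1). A single guess at the end of the trial mixes the two routes.

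The purpose of this trial is to inform a definitive one. A better-than-chance result could put sound procedures in doubt, or it could record a real leak without showing where it arose.

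**Working it through.** The article gives no figure for this test, so there is nothing to reproduce. The calculation below is an illustration.

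**Inputs from the article**
- Chance level 0.5: "Randomisation will be by random permuted blocks with a 1:1 ratio" (section 2.13).
- Number of guesses *n*: 40 randomised (section 2.11), or the follow-up targets of 32 at week 10 and 28 at week 26 (section 1.1).

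**Assumptions, because the article gives no value**
- Test: exact binomial, one-sided, alpha 0.05.
- True standardised difference between arms *d*: 0.3, 0.5 or 0.7.
- Chance *f* that a participant's follow-up answers were seen by the guessing researcher: 0.25, 0.5 or 1.
- Masking is perfect. Where answers were seen, the researcher guesses Back-on-Track if improvement is above the midpoint between the arms. Otherwise the guess is a coin toss.

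**Step 1. Accuracy of a masked researcher**

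Where answers are seen, accuracy = Φ(*d*/2):
- *d* = 0.3: Φ(0.15) = 0.560
- *d* = 0.5: Φ(0.25) = 0.599
- *d* = 0.7: Φ(0.35) = 0.637

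Overall accuracy = *f* × Φ(*d*/2) + (1 − *f*) × 0.5. For *f* = 0.25 and *d* = 0.5 this is 0.25 × 0.599 + 0.75 × 0.5 = 0.525.

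**Step 2. Critical values**

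The smallest number of correct guesses *c* with P(X ≥ *c* | *n*, 0.5) ≤ 0.05:
- *n* = 28: *c* = 19, exact size 4.4%
- *n* = 32: *c* = 22, exact size 2.5%
- *n* = 40: *c* = 26, exact size 4.0%

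**Step 3. Probability of a better-than-chance result with masking intact**

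This is P(X ≥ *c* | *n*, overall accuracy). The three entries in each cell are for *d* = 0.3, 0.5 and 0.7.

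| *n* | exact size | quarter seen | half seen | all seen |
|---|---|---|---|---|
| 28 | 4.4% | 6%, 7%, 9% | 8%, 12%, 16% | 14%, 25%, 40% |
| 32 | 2.5% | 4%, 5%, 6% | 5%, 8%, 12% | 10%, 20%, 35% |
| 40 | 4.0% | 6%, 8%, 9% | 9%, 13%, 19% | 16%, 31%, 50% |

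**Step 4. What timing changes**

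A guess made before any follow-up answer is seen corresponds to *d* = 0. Accuracy is then 0.5 and the false rate returns to the exact size in the second column.

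**The case against.** The strongest objection concerns exposure. Online self-completion is the first-listed route, and at baseline (section 2.12.6) help is for participants who cannot complete the measures on their own. Nothing suggests that everyone will be assisted at follow-up. The 50% figure needs all 40 participants to have follow-up answers seen by a researcher, whereas the article's own targets are 32 and 28 completers. If a quarter are seen, the excess over the exact size is only about 1 to 5 percentage points. This stands, and the all-seen column must be read as an upper bound.

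The guessing model is also close to a worst case. It assumes the best cut-off, recalled at the end of the trial and always applied. The evidence cited in section 1 compares Behavioural Activation with treatment as usual. The control here adds guided self-help and weekly mood monitoring (section 2.6.2), so that evidence does not establish a difference as large as 0.7. This stands too.

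Third, masking is not among the feasibility criteria in section 1.1, no progression decision is tied to it, and no efficacy analysis is planned. This limits the severity. It does not remove the fault, because section 2.14.1 itself presents the result as a test of the procedures.

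A reader might also fault the article for not recording the reason for each guess. That is form-level detail which an article may leave to the full protocol or case record form, so its absence is not an error. The criticism rests on the timing and the decision rule, which are stated.

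**Conclusion.** The point holds as a minor one. For researcher-assisted participants, the stated timing and rule let a better-than-chance result arise from the intervention working, from disclosure, or from both, with no means of telling which.

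With *d* from 0.3 to 0.7, a one-sided alpha of 0.05 and 28 to 40 guesses, the false unmasking rate is about 4% to 9% if a quarter of participants' answers are seen. The upper bound is 10% to 50% if all are seen, against an exact size of 2.5% to 4.4%. The effect, the share seen, the alpha and the guessing rule are all assumptions. The direction needs only some assisted follow-ups, a real effect, and guesses that lean on observed improvement.

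A reader might infer that the check is likely to report failed masking, or that the trial's outcome results are biased. The article supports neither. The assisted share is unknown and may be small, and the check feeds no effect estimate and no stated feasibility criterion. What is at risk is the conclusion about masking that is carried to the definitive trial.

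**What to change.** In section 2.14.1, replace the end-of-trial guess and its test with one item on the researcher form, used only for researcher-assisted follow-ups:

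- At the first assisted follow-up, the researcher records the guess before any outcome question is asked.
- Any disclosure of allocation during that assessment or a later one is logged when it happens, with its source.
- Masking is judged descriptively, on the number and share of assisted assessments with disclosure or other allocation information, and not on a test of overall accuracy.

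This also fits section 3.3, which confines the trial to descriptive statistics.

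The cost is one form item and a wording change. There are two small downsides. The basis for the judgement is the researcher's own report, and asking for a guess may prompt speculation about allocation before later assessments.
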